## Results

This study was funded by the Austrian Research Promotion Agency (FFG, grant 866873) and was approved by the ethics committee of the Medical University of Graz, Austria. The funding body and funding source are not involved in performing the research and do not play any role in the execution of the study, data analyses, or result interpretation. All described procedures related to the equipment and software development, preliminary tests, study organization, and recruitment plans were completed. The investigators involved in the test procedure were trained to use the MR prototype and perform the entire screening procedure in joint and separate sessions. As of July 15, 2022, a total of 70 participants have been screened. Because this study describes the protocol for the implementation of the MR-enhanced multimodal screening tool, no results are currently available. Data analyses and result dissemination will be completed by September 2023.

## Discussion

### Overview

The increasing availability of AR and VR technologies provides an opportunity to translate available screening tools from the laboratory to the real world. This translation is challenging because of the current limited evidence in clinical research. Therefore, the development and testing of prototypes and research protocols are important steps in the successful application of these novel technologies in health care practice. This study described the development process and research protocol for the implementation and usability of an MR-enhanced MST for the early detection of cognitive decline in older adults.

Selection of the single assessments included in this MST was based on their validity and reliability in detecting cognitive changes in healthy older adults and individuals with diagnosed cognitive impairments. The screening tool was tested in the previous phase of the SCOBES-AR project. Some of these assessments are performed for the first time in this way using MR technologies, which require integrated multidisciplinary knowledge and the development and testing of several software models.

The user-centered approach for the development of the software prototype was based on the collaboration between engineers (digital media specialists, information and communication specialists, and software developers) and end users (therapists and researchers with different expertise areas as well as older adults). Common challenges during the software design process were related to appropriate implementation of the different assessments with the MR technologies, documentation of results, and provision of guidelines for the therapists on how to use the different software and hardware products. The extensive exchange between engineers and users enabled the development of easy-to-use AR and VR software with reliable technical quality and attractive designs. This exchange enables a smooth transition from technical to clinical research settings, where the developed prototype will be applied for screening older adult test participants and further evaluated.

### Strengths and Limitations

We designed this study to compare the results of the MST (block B) to those of the MR-MST (block C). The performance in the first block may facilitate the performance in the second block. To minimize the “learning effect,” these blocks were randomized among participants. As the entire screening procedure has a duration of approximately 130 minutes, participants may experience cognitive fatigue, which could influence the results of the tests. The effect of possible cognitive fatigue was minimized by providing a resting break between the blocks and frequently obtaining feedback from participants. The order of assessments in blocks B and C was selected to ensure maximum convenience and time efficiency when changing from assessments performed using AR to those performed using VR in block C.

Another limitation of this study protocol is related to the fact that the experiments are performed at different times of the day (eg, in the morning and afternoon) and by different investigators. To reduce the impact of circadian rhythms on cognitive performance, we avoided testing in the early morning and late afternoon. To ensure standard testing conditions, all involved investigators obtained the same training using the AR and VR technologies and performed the screening procedure.

One strength of this study is that the assessments performed with VR included familiar situations and daily life activities (eg, crossing a street, shopping in a grocery store) in which immersion into the virtual world created a cognitive experience that aligned with real-life demands. The MR-enhanced assessments were designed to resemble the assessments performed with pen and paper as much as possible. We are aware that the results of MR-enhanced MST may not be directly comparable to those of the MST because of the specificity of the AR and VR equipment and environment. These findings will shed more light on the extent, art, and origin of possible differences, which will enable further adaptations and optimizations of the prototype.

Usability is another important consideration in establishing screening tools involving novel technologies. Therefore, this study describes the usability evaluation of the developed MR prototype. Feedback will be collected from the users (investigators and clients) via observations (video observations of the screening procedure) and questionnaires. Usability experts will focus on the users’ cognitive activities related to their specific goals and understanding when executing screening using the MR prototype. This approach should reveal possible limitations and user disadvantages. Notably, outlining the particular needs of improvement will encourage further optimization to enable further application of the MR-enhanced screening tool in therapeutic settings.

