## Methods

### Study Design, Participants, and Recruitment Procedure

This study developed a protocol for a single-center observational crossover design study. Male and female volunteers (N=100) aged 60 to 75 years were recruited from the pool of participants who had participated in the previous phase of the project. The volunteers were invited to a second visit at the Health Perception Lab, FH JOANNEUM University of Applied Sciences. Assuming that the effects were larger than the previous project phase, an effect size of 0.35 was selected. Therefore, with α=.05 and β=.95, a sample size of approximately 100 participants was considered sufficient for this study. Feasibility reasons and recruitment experience were also considered for the laboratory setting and geographical region. The recruitment and enrolment process for participants with stringent inclusion criteria (ie, age 60-75 years; absence of movement; and visual, auditory, neurocognitive, and psychiatric disorders) lasted from March 2022 to April 2022. For recruitment, participants were contacted by email or telephone to obtain consent and make preliminary agreements for participation. The study procedure, including the application of the respective information and technology devices, was presented to the volunteers. Participants were excluded from the study if they developed 1 or more of the conditions described in Textbox 1.

Study exclusion criteria.Clinical diagnosis of mild cognitive impairment or dementiaClinical diagnosis of mental illness (eg, depression, psychosis)Reduced mobility (eg, walking aid, wheelchair)Aided hearing or visual impairmentParticipation in any other cognitive training study within the last 6 monthsPresent guardianship according to the provisions of the Austrian adult protection law

All selected volunteers are tested once with the MST and once with the MR-MST in a randomized order. An independent investigator executed the randomization plan using a computer-generated random numbers table.

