### Study Procedure

At the beginning of the study, the investigator clarifies in detail the screening procedure and COVID-19–related hygiene measures and obtains signed written informed consent from the volunteers. The screening procedure for each participant consists of 3 blocks (see Figure 1). Anthropometric, sociodemographic, and risk factor data are collected in the first block (A). The Brief Smell Identification Test (B-SIT) [23], Food Frequency Index (FFI) [30], and Dementia Detection Test (DemTect) are also performed in block A using a laptop computer as well as pen and paper. The Dual-Task Assessment (DTA) [25,31,32], Trail-Making Test (TMT) [33], Reaction Time Test “Match 4 Point Test” [34], and Erlangen Test of Activities of Daily Living in Persons With Mild Dementia or Mild Cognitive Impairment (ETAM; parts transport and finances) [34] are performed in the second block (block B) using software as well as pen and paper. The same assessments from block B are performed in the third block (block C) using MR technologies, tailor-made MR software, and suitable AR and VR hardware. Prior randomization determines the order in which participants perform blocks B and C.

The entire testing procedure lasts approximately 130 minutes, including a 10-minute break between blocks B and C. Trained project staff conduct the study. A medical doctor acting as the clinical investigator is available to the participants for consultation to answer questions related to their cognitive health.

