### Outcome Parameters and Data Analysis

Statistical analyses will be performed to identify possible correlations between the different components of the MST and MR-enhanced MST. Spearman rank correlations (Spearman ρ) or product-moment correlations (Pearson correlations) will be calculated, depending on the distribution of the collected data. Multiple regression analyses will be conducted for cases of strong effects in the correlation between the MST and MR-enhanced MST. Descriptive statistics of the data will be presented as means and SDs. The level of significance is set at α=.05. The statistical data will be evaluated using SPSS (IBM Corp).

For usability assessment, usability experts will collect and analyze data from the video observations and questionnaires. The video observations will be evaluated using “Eisenhower's Urgent/Important Principle” [78]**,** in which items are classified as “not urgent” to “urgent” and as “not important” to “important.” The “urgent” and “important” items indicate higher needs of improvement. The questionnaires addressing the personal experiences with the screening procedure are based on a 5-point Likert scale, where 1 indicates “very good usability.”

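### Block order is randomised against learning, but the planned correlations carry no order term, so a same-direction order effect would attenuate them

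*Protocol article*

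**What the plan says.** Under Study Design, Participants, and Recruitment Procedure: "All selected volunteers are tested once with the MST and once with the MR-MST in a randomized order". Under Study Procedure: "Prior randomization determines the order in which participants perform blocks B and C". Both blocks fall in one session, "including a 10-minute break between blocks B and C".

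Strengths and Limitations gives the reason for randomising: "The performance in the first block may facilitate the performance in the second block". Randomised order is offered as the means of keeping this learning effect small. Fatigue is named separately and is addressed by the rest break and by asking participants for feedback.

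Outcome Parameters and Data Analysis states the main analysis: "Spearman rank correlations (Spearman ρ) or product-moment correlations (Pearson correlations) will be calculated, depending on the distribution of the collected data". Multiple regression follows only where a correlation is strong, and its covariates are not named. Order, period and sequence are not mentioned. The Abstract and Strengths and Limitations also announce a comparison of MR-MST results with MST results, but the analysis section names no test or estimate of a difference.

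**The concern.** The stated remedy and the stated analysis do not fit together. With randomised order, about half the participants do MR-MST second and half do MST second. If being second helps, the first group is raised on MR-MST and the second on MST. Pooling the groups then mixes two clouds of points shifted in opposite directions. That adds negative covariance and inflates both variances, so a positive correlation shrinks.

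The correlation between the tools is the main quantity in the analysis section, and it appears to be what the sample size rests on. An attenuated value would make the prototype look less related to the MST than it is. The follow-up regression cannot repair this, because it is triggered by the unadjusted correlation being strong.

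**Working it through.** **1. The plan's own figure.** Inputs: "an effect size of 0.35 was selected" and "with α=.05 and β=.95, a sample size of approximately 100 participants was considered sufficient for this study". The metric of the effect size and the sidedness of the test are not stated. Read 0.35 as a correlation, .95 as power and the test as two-sided:

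n = ((z₀.₉₇₅ + z₀.₉₅)/atanh(.35))² + 3 = ((1.960 + 1.645)/0.3654)² + 3 = 100.3.

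Power at n = 100 is 94.9%. Other readings fit less well: a one-sided correlation test needs 85, a paired t test with standardised difference 0.35 needs 109 (two-sided) or 90 (one-sided), and two independent means need 213 per group. So about 100 is reproduced as a test of r = .35.

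**2. Order effect in the pooled correlation.** Assume orders of equal size (the ratio is not stated), unit SD within each order, and true correlation ρ. MST gains λB when done second and MR-MST gains λC when done second. Across the two orders the means lie ±λ/2 from their average, in opposite directions for the two tools. This contributes covariance −λBλC/4 and variances +λB²/4 and +λC²/4:

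r = (ρ − λBλC/4) / √((1 + λB²/4)(1 + λC²/4)).

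With equal gain λB = λC = δ: r = (ρ − δ²/4)/(1 + δ²/4).

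**3. Numbers.** The size of δ is an assumption throughout. Power is by Fisher z at n = 100, two-sided α = .05.

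| δ (SD) | pooled r, ρ = .35 | power | n for 95% power |
|---|---|---|---|
| 0.1 | .347 | 94.5% | 103 |
| 0.2 | .337 | 93.2% | 109 |
| 0.3 | .320 | 90.5% | 121 |
| 0.5 | .271 | 78% | 172 |
| 0.8 | .164 | 37% | 479 |

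Example, δ = 0.5: (.35 − .0625)/1.0625 = .271. At ρ = .70 the same δ gives (.70 − .0625)/1.0625 = .60.

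Simulation at n = 100 and ρ = .35 agrees. Spearman falls from .332 without learning to .303 at δ = 0.3 and .254 at δ = 0.5. The Pearson correlation after removing order-specific means stays at about .35, with power about 95%, for δ from 0.3 to 0.8.

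**4. When the direction changes.**
- Learning in one order only (0.5 SD): .35/√1.0625 = .340.
- Opposite signs (λB = 0.5, λC = −0.5): (.35 + .0625)/1.0625 = .388, an increase.
- Net effect zero in both orders: no bias.

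**5. Differences.** The variance of an unadjusted difference is 2(1 − ρ) + (λB + λC)²/4. With equal δ the standard error grows by √(1 + δ²/(2(1 − ρ))). For δ = 0.5 this is √(1 + .25/1.3) = 1.09 at ρ = .35 and √(1 + .25/.6) = 1.19 at ρ = .70. Separately, unequal gains bias the mean MST minus MR-MST difference by (λB − λC)/2 even with equal groups: 0.25 SD if only one order gains 0.5 SD.

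**The case against.** The strongest reply is that the learning effect is acknowledged as a possibility in a limitations section, with no size attached, and that it may be small. This stands. At 0.2 SD or less the loss is slight, and the tasks differ enough between blocks that one δ will not fit every measure.

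A second reply is that this is a condensed article. A fuller plan might adjust for order, and the unnamed regression covariates might include it. This stands in part: one cannot say that order is missing from every analysis. But the correlations are described specifically, without an order term, and the regression is conditional on them.

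A reader might infer more than the document supports:
- That the correlations are certain to be too low. The downward direction needs order effects of the same sign in both sequences. Fatigue, which the article also names, works against learning.
- That randomisation is presented as the remedy for fatigue too. It is tied only to learning.
- That limits of agreement would be widened. None are planned.
- That chance imbalance between the order groups adds a further bias to the mean difference. Under simple randomisation that error has expectation zero and is already part of the inflated variance in step 5.

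**Conclusion.** The point holds as a should-fix. Randomising order does what it can for the comparison of means under equal carry-over, but it does not protect a pooled correlation. If learning acts in the same direction in both orders, the planned correlation is attenuated: negligibly at 0.1 to 0.2 SD, and materially at 0.5 SD, where .35 becomes .271 and power drops from 95% to 78%.

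These sizes rest on an assumed δ, equal gains, equal order groups, and reading the effect size of 0.35 as a correlation. Direction and size are therefore unknown in advance, which is itself a reason to estimate the order effect. A must-fix rating is not supported: the usual error would understate an association, and adjustment remains possible as long as the randomised order is kept with the data.

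**What to change.** In Outcome Parameters and Data Analysis, or in the full analysis plan:

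1. Report each MST to MR-MST correlation as a partial correlation given the randomised block order, Pearson or rank-based as the data require.
2. Include block order in the follow-up regressions.
3. Include a period term in any estimate of the MR-MST minus MST difference.
4. Report the estimated order effect for each tool, and the correlation within each order, as description only. With about 50 per order these are imprecise: the standard error of a tool's order effect is about √(1/50 + 1/50) = 0.2 SD.
5. State that unequal carry-over between the two orders would bias the mean difference even with equal groups, and that the period term does not remove it.

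The cost is wording and one degree of freedom per analysis. No new data are needed, and the article reports that no results were yet available.

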### Conclusions

The development and application of the described MR-enhanced prototype for the screening of early cognitive decline in older adults is an innovative and demanding process. Establishment of the respective methodological procedures is a saliant step toward identifying the best practices. The results of the study will provide more information on the usability, utility, and applicability of AR- and VR-enhanced screening tools, which may encourage further development of these models and their use in therapeutic settings.

## Abbreviations

AR: augmented reality
B-SIT: Brief Smell Identification Test
DemTect: Dementia Detection Test
DTA: Dual-Task Assessment
ETAM: Erlangen Test of Activities of Daily Living in Persons with Mild Dementia or Mild Cognitive Impairment
FFI: Food Frequency Index
MCI: mild cognitive impairment
MR: mixed reality
MST: multimodal screening tool
SCOBES AR: Smart Cognition & Behaviour Screening powered by Augmented Reality
TMT: Trail-Making Test
VR: virtual reality
